### Secondary outcomes

(xxii)Plasma HIV viral load will be measured at baseline, and at weeks 4, 8. 12, 16, 20, 28 thereafter.(xxiii)High risk sexual activity will be assessed by survey of number of sexual partners, condomless sex, and screening of all orifices for chlamydia, gonorrhea and blood for syphilis.

### Process measures

(vii)Participants’ feedback will be measured on ID-Cap at week 4, 8, 12, 16 and 20, and SBDOH intervention at weeks 4, 8, 12, 16, 20 and 28.

### Statistical analyses

We will use α < 0.05 as the significance level for statistical testing, and will use appropriate corrections (e.g., Bonferroni correction) for multiple comparisons to ensure that the effective type I error remains at 0.05 level. Statistical analyses will be conducted on an intention-to-treat sample using the SAS and R statistical software.

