**Methods:**

In this protocol paper, we describe the design and procedures for a National Institutes of Health-funded randomized controlled trial that tests an innovative, integrated intervention combining the latest pill ingestible sensor system (the ID-Cap from etectRx) and strategies to address SBDOH. The intervention will trigger real-time actions to rapidly address SBDOH-related barriers when pre-specified patterns of poor adherence are detected (antiretroviral doses missed on three days within a five-day period). A cohort of 110 PLWH who have, or are at high risk for, sub-optimal adherence will be recruited from an HIV clinic in Los Angeles County. Participants will be randomized into the ingestible sensor intervention arm or the usual care arm. The intervention will run for 16 weeks, followed by a 12-week post-intervention period to evaluate sustainability. The primary outcomes are acceptability of the integrated intervention, frequency and timeliness of SBDOH intervention, level of challenges of SBDOH in HIV treatment, adherence to ART measured by ID-Cap system, and self-reported medication adherence. Secondary outcomes are plasma HIV viral load and high risk sexual activity,

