**Fig. 1 Fig1:**
[figure not shown]
SPIRIT figure for the trial Medical. STI and Treatment History

The overall flow of the study is shown in Fig. 2. This study is an open-label unblinded randomised control trial. Participants will be randomly assigned by 1:1 allocation to either: (1) the ISS-SBDOH arm, which will include training on how to use the ingestible sensor system (the ID-Cap from etectRx), data collection procedures, and schedules; or (2) the Usual Care (UC) arm, which will not use of ID-Cap system. On-boarding procedures will be done for both study arms. In the first 20 weeks, we will collect data on primary end points of acceptability of the ISS-SBDOH intervention, frequency and timeliness of SBDOH intervention, level of challenges of SBDOH in HIV treatment, and adherence to ART; the secondary end points will include viral load, high risk sexual activity and frequency of detectable sexually transmitted infections (STIs); and other measures. Durability of any observed effects from the ISS-SBDOH intervention will be evaluated during a 12-week post-ID-Cap system follow-up period. The trial will be conducted in accordance with the guidelines for Good Clinical Practice (GCP) and will satisfy Consolidated Standards of Reporting Trials (CONSORT) reporting conventions [27].

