## Outcomes

### Primary outcome

(i)Acceptability of the integrated intervention will be measured at baseline, and around week 4, 8, 12, and 16, evaluated by quantitative measures interviews. The items in the quantitative measure will be rated on a five-point Likert scale ranging from very strongly disagree to very strongly agree. Acceptability will be measures in terms of: overall satisfaction (would recommend to friend, would use outside of study setting, satisfied with system), utility, and specific items such as helpfulness and convenience. In addition, we will ask participants to rate items specific to the ID-Cap system (comfort of wristband, comfort receiving text messages).(ii)Frequency and timeliness of SBDOH intervention, level of challenges of SBDOH in HIV treatment will be measured at baseline, and around week 4, 8, 12, 16, 20, and 28. We will collect SBDOH measures, such as economic stability (e.g., food security), health (e.g., gap in health coverage), neighborhood and built environment (e.g. transportation needs), social and community context (e.g., violence, and criminal justice involvement), and substance and alcohol use, sexual behavior, and other health related behaviors. Challenges of SBDOH will be measured as the count of SBDOH issues one is facing, and the degree of each issue (e.g., low/medium/high with housing challenge determined by nurse or care coordinator) with summary scores. Frequency and timeliness of SBDOH intervention are measured as number of sessions, and time to first, and subsequent sessions, if applicable, from baseline, and others. This information will also be collected when intervention is triggered by the monitoring system.(iii)Adherence to ART measured by ID-Cap system for 16 weeks.(iv)Self-Reported Medication Adherence [34]. We will use a widely used measure of percent of prescribed dose taken during the preceding seven days. We will also measure patterns of dosing (e.g., patterns of consecutive missed doses in the past two weeks).

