### Sample size calculation

Sample size calculation and power analysis were conducted based on the primary and secondary end points. For Aim 1, 55 subjects to be recruited in the ISS-SBDOH arm and 55 in the UC arm enable us to obtain stable point estimates and test the hypotheses for acceptability of the intervention program using one sample binomial approach. For the frequency and timeliness of SBDOH intervention and level of challenges, group sample sizes of 55 in the ISS-SBDOH arm and 55 in the UC arm will enable us to detect a difference as small as 0.5 in a continuous outcome (a medium Cohen’s effect size) with 80% power, and a significance level of 0.05 using a two-sided two-sample t-test. For Aim 2, using repeated measures analysis with intra-subject correlation of 0.1, a type I error of 0.05, a type II error of 0.2 (or 80% power), and average number of available data points 3.5, out of 5 data points (baseline, weeks 4, 8, 12, 16), 55 subjects in each of the two arms will enable us to detect a difference as small as 0.29 in standardized unit of the outcomes (e.g., adherence to ART) between the two arms, which is statistically and clinically meaningful. For Aim 3, for the binary outcome variable of viral suppression, using repeated measures analysis with similar set-up as Aim 2, the sample size of 55 participants in each of the 2 arms will be able to detect a 9% difference (or an odds ratio of 2.7) between the 2 arms (assuming 85% viral suppression at week 16 for control arm) and this effect size is considered clinically meaningful. Thus, the planned sample size should be sufficient for the proposed analyses.

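### Power is computed at an uncorrected 0.05 although the plan promises a multiplicity correction and has several unranked between-arm primary outcomes

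*Protocol article*

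**What the plan says.** Under Statistical analyses the protocol article states "We will use α < 0.05 as the significance level for statistical testing" and adds that it "will use appropriate corrections (e.g., Bonferroni correction) for multiple comparisons to ensure that the effective type I error remains at 0.05 level". Bonferroni is an example there. The section does not name the family of tests or their number.

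The abstract reads "The primary outcomes are acceptability of the integrated intervention, frequency and timeliness of SBDOH intervention, level of challenges of SBDOH in HIV treatment" and goes on to ID-Cap adherence and self-reported adherence, which makes five entries. The Primary outcome section groups them into four numbered items, the second of which joins frequency, timeliness and level of challenges ("Frequency and timeliness of SBDOH intervention, level of challenges of SBDOH in HIV treatment will be measured at baseline"). Neither place gives a lead outcome, an order or a split of alpha.

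Under Sample size calculation, Aim 1 has "55 subjects to be recruited in the ISS-SBDOH arm and 55 in the UC arm" and is said to "detect a difference as small as 0.5 in a continuous outcome" "with 80% power, and a significance level of 0.05 using a two-sided two-sample t-test". Aim 2 uses a type I error of 0.05, 80% power, an intra-subject correlation of 0.1 and on average 3.5 of 5 data points, giving a detectable standardized difference of 0.29. Aim 3 uses a similar set-up. The section ends by calling the planned size sufficient for the proposed analyses.

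**The concern.** The proposed analyses include a correction that the power calculation leaves out. If several between-arm primary outcomes share an overall 0.05 by a Bonferroni-type rule, each is tested at a smaller alpha, and 80% power at 0.05 does not describe the trial that will be run.

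The adherence comparison is the one most exposed. It would share alpha with the number and timing of SBDOH sessions, which the sensor trigger drives directly. The trial would then either have a much lower chance than stated of detecting the effect it calls clinically meaningful, or would come under pressure to relax the promised error control. In an open-label trial with unranked primary outcomes, that choice should be settled before data are seen.

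**Working it through.** **Which tests are between-arm.** Acceptability is a one-sample binomial test in the intervention arm (Aim 1). ID-Cap adherence is measured only in the intervention arm (Schedule of events and assessments). That leaves level of challenges, frequency, timeliness and self-reported adherence: k = 4 tests, or k = 3 if frequency and timeliness are analysed as one.

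**Inputs from the article.** 55 per arm, 1:1 allocation; Aim 1 d = 0.5, two-sided t-test; Aim 2 difference 0.29, correlation ρ = 0.1, m = 3.5 data points. Sidedness is not stated for Aim 2; two-sided is assumed.

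**Step 1: the stated 80% at 0.05.**

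- Aim 1: noncentrality = 0.5 × √(55/2) = 2.622, with 108 degrees of freedom and critical value 1.982. Power is 73.8%. The detectable difference at 80% power is 0.539, and d = 0.5 needs 64 per arm.
- Aim 2: variance factor = [1 + (m − 1)ρ]/m = (1 + 2.5 × 0.1)/3.5 = 0.3571. SE = √(2 × 0.3571/55) = 0.1140. 0.29/0.1140 = 2.545, and power = Φ(2.545 − 1.960) = 72.1%. The detectable difference is (1.960 + 0.842) × 0.1140 = 0.319.
- The 0.29 is roughly matched only with all 5 data points (variance factor 1.4/5 = 0.28, SE 0.1009, power 82.0%) or with a one-sided test at 3.5 points (81.6%).

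So part of the gap to 80% exists before any correction.

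**Step 2: the corrected alpha, 0.05/k.** The same formulas, with the critical value changed (normal values 2.241, 2.394 and 2.498 for k = 2, 3 and 4; t values 2.273, 2.432 and 2.540).

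| k | alpha | Aim 1 power, d = 0.5 | Aim 1 detectable | Aim 2 power, 0.29, m = 3.5 | Aim 2 detectable | Aim 2 power, m = 5 |
|---|---|---|---|---|---|---|
| 1 | 0.05 | 73.8% | 0.539 | 72.1% | 0.319 | 82.0% |
| 2 | 0.025 | 63.7% | 0.595 | 61.9% | 0.351 | 73.6% |
| 3 | 0.0167 | 57.7% | 0.625 | 56.0% | 0.369 | 68.4% |
| 4 | 0.0125 | 53.4% | 0.646 | 51.9% | 0.381 | 64.7% |

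For 80% power at d = 0.5, the t-test needs 86 per arm at k = 3 and 91 at k = 4, against 55 planned.

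**Step 3: the correction on its own.** Take the stated 80% at face value, so that the signal is 1.960 + 0.842 = 2.802. Power is then Φ(2.802 − z), where z is the corrected normal critical value: 71.2% at k = 2, 65.8% at k = 3 and 61.9% at k = 4. The correction alone therefore costs about 14 to 18 percentage points at three or four tests.

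**The case against.** The article does not say that the correction runs across the primary outcomes. It speaks of multiple comparisons and gives Bonferroni as an example. Aim 1 also contains an obvious family within one outcome: the same binomial test at baseline and four later visits. Control within each outcome or aim would fit the wording, a stepwise method would lose less than Bonferroni, and in a fixed sequence the first test keeps the full 0.05. Defining the family is commonly left to an analysis plan, which is not shown.

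Most of this stands. It rules out two stronger readings that a reader might infer. One is that the two sections cannot both hold: they could be reconciled by a testing order, although none is stated. The other is that power is near 50% because the correction was omitted. Five-test figures at that level count two outcomes that exist in one arm only, and part of the fall is the separate shortfall already present at 0.05.

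The objection does not rescue the sample size statement. The article promises overall control at 0.05, ranks no primary outcome, and applies the full 0.05 throughout. An equal Bonferroni split over even two tests leaves about 71% from a true 80%.

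**Conclusion.** The concern holds in a limited form: the sample size section makes no allowance for the correction that the analysis section promises. For three to four between-arm tests under Bonferroni, power at the article's own effect sizes is about 58–53% for Aim 1 and 56–52% for Aim 2. About 74% and 72% is the starting point at 0.05; the rest of the fall comes from the correction. Readings more favourable to Aim 2 still fall short: all five data points give about 68–65%.

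These figures assume two-sided tests, 55 analysed per arm and an equal Bonferroni split. A smaller family or a less conservative procedure would lose less. The direction is secure for an equal split; the exact size waits on a family that the article does not fix.

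**What to change.** In Sample size calculation, restate power and detectable differences at the corrected alpha for the family the trial will use. Show the uncorrected 72–74% separately, so that the two shortfalls are not confused. Name the between-arm primary tests in that family and keep acceptability and ID-Cap adherence outside it, as one-arm outcomes.

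Alternatively, prespecify a single lead between-arm outcome, or a fixed testing order with one test per step. Frequency and timeliness would then be separate steps, because two tests at 0.05 within one step would not hold the overall level. The order is the sponsor's choice. The text should say that the first test at 0.05 still has only about 72–74% power with 55 per arm.

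Either change costs about a paragraph and needs no new data collection. The drawback of an order is that an outcome lower down cannot be claimed if an earlier one fails. The drawback of restating power is that the detectable differences become visibly larger, about 0.63–0.65 SD for Aim 1 and 0.37–0.38 SD for Aim 2 at three to four tests, and the claim that the size is sufficient would have to be argued on those terms.

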### AIM 1. Evaluate the acceptability, frequency and timeliness of SBDOH intervention, and level of challenges of SBDOH in HIV treatment among PLWH

We hypothesize that greater than 75% of the participants in the ISS-SBDOH arm will rate the intervention as fitting their routine activities of daily life. To test this hypothesis, we will perform analyses in two levels: (1) Obtain point estimates of ratings about the intervention and conduct one group binomial test of the proportion with answers that indicates a fit (or better fit). This will be done at each of the time point of baseline, and weeks 4, 8, 12, and 16; (2) Generalized linear mixed models (GLMM) will be used to model the changes of ratings over time controlling characteristics (e.g., demographics, SBDOH, regimen type (single/multiple pill), and viral load). GLMM can model not only global fixed effects (e.g., the regimen type), but also random effects (e.g., change over time within a person). We also hypothesize that the ISS-SBDOH arm will have significantly higher frequency and better timeliness of the SBDOH intervention sessions than the UC arm; and the ISS-SBDOH arm will have lower level of challenges of SBDOH over time than the UC arm. To test this, we will use GLMM to model the number of challenges of SBDOH over time through parameter estimate of time (fix effect) in the model.

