### AIM 2. Evaluate the efficacy of the integrated intervention of ISS-SBDOH for monitoring, facilitating and improving adherence to ART

We hypothesize that the ISS-SBDOH arm will have significantly higher mean adherence to ART than the UC arm. GLMM will be used modeling adherence to ART across the contact periods. An arm (ISS-SBDOH or UC) dummy variable will be included in the model to test if the level of adherence is different between the two arms. If the distributions are substantially skewed, we will evaluate categorized clinical cut-off values using generalized estimating equation (GEE) analysis.^95^ For possible non-linear relationships between outcomes and time, we will use generalized additive mixed model (GAMM). The trend of adherence changes before and after 16 weeks will be compared. In addition, we will evaluate group differences in demographics (e.g., gender) and control for these variables in modeling. We also hypothesize that the use of ISS-SBDOH will be associated with lower levels of non-adherence (e.g., fewer single missed doses, a shorter maximum duration of taking no doses) than the UC arm over time. We will make full use of machine learning and data mining methods, including classification and regression trees (CART), random forests, XGBoost, Generalized Additive Models, to identify non-adherence patterns in the data. We will use GLMM/GAMM to model adherence between ISS-SBDOH and UC arm over time to determine if it differs between arms. The GAMM modeling will graphically show the change trend over time. We will also evaluate the distribution of DTEs and their changes over time in the ISS-SBDOH arm. We hypothesize that the differences in adherence between the ISS-SBDOH and the UC arms will be sustained during the 10-week post-intervention period. GLMM/GEE and GAMM will be used to model adherence between the two arms, including parameterization that can distinguish the 16-week trial and 12-week follow-up periods.

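### Bonferroni, the only multiplicity correction the protocol names, is valid but dominated by Holm's step-down procedure, which never rejects less at the same family-wise 0.05

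*Protocol article*

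**What the plan says.** The Statistical analyses section of the protocol article sets the level, "We will use α < 0.05 as the significance level for statistical testing", and then says the analysis "will use appropriate corrections (e.g., Bonferroni correction) for multiple comparisons to ensure that the effective type I error remains at 0.05 level". No other correction is named anywhere in the article, and the tests that form a family are not listed.

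Several tests could fall under that sentence. The abstract states: "The primary outcomes are acceptability of the integrated intervention, frequency and timeliness of SBDOH intervention, level of challenges of SBDOH in HIV treatment", followed by sensor-measured and self-reported adherence. Aim 1 expects that "the ISS-SBDOH arm will have significantly higher frequency and better timeliness of the SBDOH intervention sessions than the UC arm", and also a lower level of challenges. Aim 2 adds: "We hypothesize that the ISS-SBDOH arm will have significantly higher mean adherence to ART than the UC arm". Acceptability is tested separately, in the intervention arm only, by a one-group binomial test: "This will be done at each of the time point of baseline, and weeks 4, 8, 12, and 16".

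**The concern.** Bonferroni tests every hypothesis in a family of m at 0.05/m, whatever the other tests show. Holm starts at the same threshold but relaxes it after each rejection. It gives the guarantee the protocol asks for, with no added assumption and no added data. If the analysis follows the named example, a real effect on a second, third or fourth outcome could be called non-significant where Holm would have declared it.

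The trial has 110 participants, and the power statements in Sample size calculation that give a significance level use 0.05 without a multiplicity adjustment. There is no reserve to pay for a correction less efficient than it need be. What is at stake is power on outcomes after the first rejection, not the validity of the tests.

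**Working it through.** **Why Holm dominates.** Order the p-values from smallest to largest. Holm compares the j-th with 0.05/(m − j + 1) and stops at the first failure. For m = 4 the thresholds are 0.0125, 0.0167, 0.025 and 0.05, against 0.0125 four times for Bonferroni.

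- *Never rejects less.* If a p-value is at most 0.05/m, so are all smaller ones, and each Holm threshold is at least 0.05/m. Holm therefore rejects it too.
- *Same error control.* With m0 true nulls, the first true null is reached at step m − m0 + 1 at the latest, where the threshold is at most 0.05/m0. A false rejection requires the smallest true-null p-value to be at most 0.05/m0. By the union bound its probability is at most m0 × 0.05/m0 = 0.05, under any dependence.

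**Inputs from the article.** Sample size calculation has "group sample sizes of 55 in the ISS-SBDOH arm and 55 in the UC arm" to "detect a difference as small as 0.5 in a continuous outcome (a medium Cohen’s effect size) with 80% power", two-sided at 0.05.

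**Assumptions, because the article does not define the family.** m = 4 (session frequency, timeliness, level of challenges, self-reported adherence), with m = 3 to 6 as a range; equicorrelated normal test statistics with correlation 0 to 0.5. Sensor-measured adherence is not counted as a between-arm comparison, because it is collected only in the intervention arm.

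**The plan's own figure first.** For d = 0.5 and 55 per arm, the expected test statistic is 0.5 × √(55/2) = 2.622. Two-sided power is Φ(2.622 − 1.960) = 0.746 (0.738 with the t-distribution), not the stated 80%, which needs an expected statistic of 2.802. That discrepancy is a separate matter. Both starting points are carried below.

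**Bonferroni, m = 4.** The critical value at two-sided 0.0125 is 2.498. Power per test is Φ(2.802 − 2.498) = 0.619 from the stated 80%, and Φ(2.622 − 2.498) = 0.549 from d = 0.5.

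**Bonferroni against Holm by simulation** (m = 4, 300,000 to 400,000 draws per setting; average power over the real effects; ranges span correlation 0 to 0.5):

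| Real effects of 4 | 80% unadjusted: Bonferroni | Holm | d = 0.5, 55 per arm: Bonferroni | Holm |
|---|---|---|---|---|
| 4 | 62% | 71-73% | 55% | 64-65% |
| 3 | 62% | 67-68% | 55% | 60% |
| 2 | 62% | 64-65% | 55% | 57% |
| 1 | 62% | 62% | 55% | 55% |

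- In no draw did Bonferroni reject something that Holm did not.
- The chance of at least one rejection is identical in every setting (0.89 to 0.98 with four real effects at 80% unadjusted power).
- With all nulls true, family-wise error is the same for both: 0.049 at correlation 0 and 0.043 at 0.5. With one real effect and three nulls, Holm's reaches at most 0.044.

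**Other family sizes, all effects real, 80% unadjusted.** m = 3: 66% against 74-75%. m = 5: 59% against 69-71%. m = 6: about 57% against 67-68%. Over m = 3 to 6 and both starting points, Holm adds about 8 to 12 points.

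**The case against.** The strongest reply is that the article has not chosen Bonferroni at all. Its commitment is to hold type I error at 0.05. Bonferroni is an illustration, Holm already qualifies as an appropriate correction, and the exact procedure is a usual matter for the analysis plan. This stands in large part. A reader might infer that the trial is bound to Bonferroni, or that the article is wrong on multiplicity. Neither is supported: the wording leaves the method open, and Bonferroni does control the error. What remains is that the one method named is a dominated one, and that the choice is better settled before p-values are seen.

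A second reply is that the gain can be made to look larger than it is. This also stands. The 71-73% needs all four effects to be real in a family the article does not define, and starts from an 80% that d = 0.5 with 55 per arm does not deliver. A reader might also point to the chance of showing all four effects (15-31% with Bonferroni, 38-53% with Holm), but nothing in the article requires success on all four. Nor does it say that the outcomes are correlated. It hypothesises benefit on each, and higher correlation slightly narrows Holm's gain in average power (72.6% at correlation 0, 71.0% at 0.5).

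**Conclusion.** The point holds as an efficiency improvement. Holm meets the article's stated aim under any dependence and is never worse than Bonferroni; that part rests on no assumption. The size of the gain does rest on assumptions. With four comparisons it is about 9 to 11 points of average power if all effects are real, 2 to 3 points if two are, and 0.1 to 0.2 points if one is. It is nil for the chance of at least one rejection. Starting from d = 0.5 with 55 per arm, the levels are lower but the pattern is the same. Nothing here shows an inflated error rate or an invalid test.

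**What to change.** In Statistical analyses, replace the bracketed Bonferroni example with: *Holm's step-down procedure at family-wise two-sided 0.05 within each family of multiple comparisons*. State that the between-arm primary comparisons form one family.

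The words *within each family* matter. The present sentence covers multiple comparisons in general. Confining Holm to the between-arm primary comparisons could drop the promised correction elsewhere, for example for the acceptability tests repeated at five time points in Aim 1.

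The cost is one phrase, with no change to sample size, data collection or participants. The small downside is that simultaneous confidence intervals are less direct than with Bonferroni; unadjusted 95% intervals can be reported beside Holm-adjusted p-values.
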